### Sample size determination

The required sample size was calculated using G*Power (version 3.1.9.7, Germany) for a two-way repeated-measures ANOVA (within-between interaction), with a significance level of α = 0.05, power (1–β) = 0.80, and four intervention groups (Control, RT, VT, RVT). The effect size was set to f = 0.40 (partial η^2^ = 0.14), which reflects a moderate-to-large effect based on prior studies assessing changes in IGF-1 expression and physical function following resistance and vibration training in older adults. The primary endpoint for power estimation was the change from baseline to 12 weeks, representing the completion of the supervised intervention. The 24-week point is considered a follow-up to assess sustainability but was not included in the power calculation. Considering a 20% dropout rate, the minimum required sample size was estimated at 73 participants [45]. Therefore, we plan to recruit 96 individuals (24 per group) to ensure adequate statistical power. In view of multiple primary outcomes and six pairwise comparisons among four groups, Holm–Bonferroni correction will be applied to adjust for potential inflation of type I error. Additionally, the hypothesis is based on additive rather than synergistic effects between RT and VT. Hence, interaction effects were not included in the sample size model but will be explored post hoc.

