### Randomization and blinding

After acquiring the signed consent forms, 96 participants will be screened for eligibility and will be randomly categorized into the RT, VT, RVT, or control group, at a 1: 1: 1: 1 ratio using computer-generated simple randomization. A reproducible random number sequence will be generated using IBM SPSS (version 27.0), and participants will be sorted in ascending order based on these numbers. Group allocation will be determined using a modulo-4 method: remainder 0 = RT, remainder 1 = VT, remainder 2 = RVT, and remainder 3 = control, ensuring equal group sizes. No baseline characteristics (e.g., age, sex) will be used as stratification factors during randomization. To minimize allocation bias, group assignments will be concealed using sequentially numbered, opaque, sealed envelopes (SNOSE), and only personnel responsible for randomization will have access to the sequence. Investigators, outcome assessors, and statisticians will remain blinded to group allocation throughout the study.

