### Statistical analysis

IBM SPSS v.20.0 will be utilized to analyze all the data. The primary outcomes will be assessed using two-way repeated-measures analysis of variance (ANOVA), with factors including time (baseline, 12 weeks, 24 weeks) and group (control, RT, VT, RVT). This approach was selected to allow direct estimation of group-by-time effects for predefined primary endpoints under a balanced design. Holm–Bonferroni adjustments will be applied for post-hoc pairwise comparisons. Missing data will be imputed via multiple imputation. Sex, along with baseline IGF-1, age, and muscle mass, will be included as covariates in analysis of covariance (ANCOVA) models to adjust for potential confounding effects. Effect sizes (partial η^2^ for ANOVA; for pairwise comparisons, the Cohen’s d with 95% confidence intervals were employed) will be categorized as small (η^2^ ≥ 0.01, d ≥ 0.2), medium (η^2^ ≥ 0.06, d ≥ 0.5), or large (η^2^ ≥ 0.14, d ≥ 0.8), accompanied by exact p-values. The 95% confidence intervals for Cohen’s d and model-based estimates will be calculated using either model-derived standard errors or the bias-corrected and accelerated (BCa) bootstrap method with 1,000 resamples, depending on distributional assumptions. To better accommodate repeated measures and potential within-subject correlations in secondary longitudinal outcomes, linear mixed-effects models will be used, incorporating random intercepts for participants and fixed effects for time, group, and their interaction. In addition, exploratory subgroup analyses stratified by sex will be conducted to evaluate potential sex-specific intervention effects. Subgroup interaction terms will be tested where appropriate, with p < 0.10 considered indicative of potential moderation. Statistical significance will be defined as p < 0.05 for all primary tests. Although the current sample size is not specifically powered to detect sex-based interaction effects, these exploratory analyses will inform the design of future sex-specific trials. All analyses will follow the intention-to-treat (ITT) principle. All randomized participants will be analyzed according to their assigned groups, regardless of protocol adherence or study completion status.

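### Holm is valid for the six pairwise comparisons but stricter than four group means require; Shaffer's divisors never reject fewer pairs at the same familywise error

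*Protocol article*

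**What the plan says.** Two sections of the protocol article fix the method.

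- **Sample size determination:** "In view of multiple primary outcomes and six pairwise comparisons among four groups, Holm–Bonferroni correction will be applied". The same section sets the planning values: "with a significance level of α = 0.05, power (1–β) = 0.80, and four intervention groups"; "The effect size was set to f = 0.40"; "The primary endpoint for power estimation was the change from baseline to 12 weeks". It also states that RT and VT are expected to act additively, not synergistically.
- **Statistical analysis:** each primary outcome gets a group-by-time repeated-measures ANOVA with four groups and three time points (baseline, 12 and 24 weeks). Then "Holm–Bonferroni adjustments will be applied for post-hoc pairwise comparisons".

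Neither section uses the logical links among the six comparisons or makes the pairwise tests depend on the ANOVA F. Neither says which time point the pairwise tests use, or whether Holm runs over six comparisons per outcome or over all 3 × 6 = 18.

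**The concern.** Holm's step-down rule compares the ordered p-values with 0.05/6, 0.05/5, 0.05/4 and so on, as if any number of the six null hypotheses could be true together. For pairwise equalities among four means that is impossible, so the second and third steps are stricter than familywise control requires.

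The trial asks whether the combination does better than its parts. Under the protocol's additive hypothesis, RVT versus RT and RVT versus VT are smaller differences than RVT versus control. They are therefore usually reached at the second step or later, where Holm is too strict. Some power for the comparisons that matter most is given up with nothing gained in error control.

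**Working it through.** **1. The plan's own figure.** Treat the 12-week change as a one-way comparison of four groups, with noncentrality N·f² on 3 and N − 4 degrees of freedom.
- N = 72: power 0.799.
- N = 73: noncentrality 73 × 0.16 = 11.68, power 0.805.

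So the stated 73 is reproduced, as the number of participants with data. Allowing for 20% dropout gives 73/0.8 = 91.25, or 92, which the planned 96 covers. (The article presents 73 as already allowing for dropout; that is a separate matter and does not affect this point.) The check uses 24 per arm, and 24 × 0.8 = 19.2, so about 19 per arm after dropout.

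**2. How many equalities can be true.** Group the four means by which are equal:

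| Pattern | True pairwise nulls |
|---|---|
| all four equal | 6 |
| three equal, one apart | 3 |
| two pairs | 2 |
| one pair, two apart | 1 |
| all different | 0 |

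Five and four true nulls cannot occur. After one rejection, at most three can remain.

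**3. Thresholds at 0.05.**

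| Step | Holm | Shaffer |
|---|---|---|
| 1 | 0.05/6 = 0.0083 | 0.05/6 = 0.0083 |
| 2 | 0.05/5 = 0.0100 | 0.05/3 = 0.0167 |
| 3 | 0.05/4 = 0.0125 | 0.05/3 = 0.0167 |
| 4 | 0.05/3 = 0.0167 | 0.05/3 = 0.0167 |
| 5 | 0.05/2 = 0.0250 | 0.05/2 = 0.0250 |
| 6 | 0.0500 | 0.0500 |

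No Shaffer threshold lies below Holm's, so Shaffer rejects everything Holm rejects. This holds whatever the effects are.

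**4. Assumed means.** In SD of the 12-week change, take control 0, RT d, VT d, RVT 2d. Additivity is from the article; equal RT and VT effects are an assumption. Then f = d·√0.5, so d = 0.40/0.7071 = 0.566 and RVT versus control is 1.13. As a second pattern, if only RVT differs, the difference is 0.40/(√3/4) = 0.924.

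**5. Power by simulation.** 200,000 or more trials per scenario; two-sided pooled-variance t tests on 4(n − 1) degrees of freedom; complete data; one outcome at 0.05. The closed test in the last column is defined under the fix.

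| Scenario | Holm | Shaffer | Closed test |
|---|---|---|---|
| Additive, n = 24, RVT vs RT | 28.1% | 32.0% | 38% |
| Additive, n = 24, at least one of RVT vs RT, RVT vs VT | 40% | 46% | 49% |
| Additive, n = 24, both | 15.9% | 18.1% | 26.5% |
| Additive, n = 19, RVT vs RT | 20.6% | 24.3% | 29% |
| Only RVT differs, n = 24, RVT vs RT | 72% | 75.5% | 78% |
| Only RVT differs, n = 19, RVT vs RT | 58.5% | 62% | 65% |

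For scale, at n = 24 the noncentrality of RVT versus RT is 0.566 × √12 = 1.96. An unadjusted test at 0.05 would have only about 49% power.

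**6. Familywise error.** With all four means equal and n = 24, it was about 4.1% for Holm and for Shaffer. Over the all-equal, 3+1 and 2+2 nulls it was at most 4.9% for both, and 5% within simulation error for the closed test. Holm never rejected a pair that Shaffer did not. In roughly 0.2% to 1% of trials Holm rejected a pair that the closed test did not.

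**7. If all 18 comparisons form one family.** After one rejection at most 3 + 6 + 6 = 15 nulls can be true, against Holm's 17. With three independent outcomes and the additive pattern in each, power for RVT versus RT is 16.5% under both methods at n = 24, and goes from 11.0% to 11.1% at n = 19.

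**The case against.** The strongest reply is that nothing is wrong. Holm is a standard, pre-specified method, named consistently in both sections, and it controls the familywise error. Preferring a somewhat more powerful valid method is a matter of efficiency. That stands, and it limits this point to a suggestion.

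Three further objections also stand in part.

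- **The family is not clear.** The sample size section gives both the multiple primary outcomes and the six comparisons as grounds for Holm. If that means one family of 18, the gain nearly vanishes and Holm is itself the protection across outcomes. Replacing it by a within-outcome test at 0.05 would remove that protection: for three independent outcomes, 1 − 0.95³ = 14%.
- **The ANOVA F cannot serve as the gate.** A reader might infer that the F test already planned can open a closed procedure at no cost. The article does not support this, because that F spans three time points while the powered contrast is the 12-week change. A difference present only at 24 weeks could make it significant while every 12-week null is true. The remaining closed tests would then have a 12-week familywise error of about 7.3% to 7.4%.
- **The size rests on assumptions.** Equal RT and VT effects are not stated. If only RVT differs, the combination contrasts are no smaller than RVT versus control. The simulation also ignores the planned covariates and multiple imputation.

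None of this touches the ordering of the two methods: for the six pairs within an outcome, Shaffer cannot do worse than Holm.

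**Conclusion.** The point holds as a modest, optional improvement. For six pairwise comparisons within one outcome, Holm is valid but needlessly strict at its second and third steps, and Shaffer's divisors remove that strictness within the same familywise limit. The gain for RVT versus RT is about 4 percentage points under the protocol's additive f = 0.40 (28% to 32% at 24 per arm, 21% to 24% at 19). It assumes equal RT and VT effects, complete data and one outcome at 0.05.

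Two stronger readings are tempting, and neither is supported. Holm is not an error in this plan, because it controls what it is meant to control. Nor does the change make the trial adequately powered to show that the combination beats its components: at about 32%, or 38% with a closed test, power stays low, mainly because of the sample size relative to these smaller differences.

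**What to change.** **Recommended change.** Under Sample size determination and Statistical analysis, replace Holm for the six pairwise comparisons within each primary outcome by Shaffer's step-down divisors 6, 3, 3, 3, 2, 1, applied at whatever alpha that outcome is allotted. Say in the same place how the error is controlled across the three primary outcomes, so that the protection the sample size section intends is kept. This costs two sentences, no participants, and no rejection that Holm would have made. Recruitment is expected to run to 30 April 2026 and the statisticians are blinded, so it can be fixed before unblinding.

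**Optional stronger version.** Use a closed test in which a pair is claimed only if all five of these are significant at the outcome's alpha:
1. the four-group F;
2. the first three-group F containing the pair;
3. the second three-group F containing the pair;
4. the 2+2 F (this pair equal and the other two groups equal);
5. the pair itself.

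All five must be on the same contrast, for example the 12-week change, and not the three-time-point interaction. This gives about 38% at 24 per arm and 29% at 19 under the same assumptions. Its costs are that each F test must be pooled over the imputed data sets, and that it occasionally loses a pair Holm would have claimed.

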**Method:**

This prospective randomized controlled trial will be conducted among 96 participants, aged between 65 and 80 years. In participants, sarcopenia diagnosis will be confirmed based on the Asian Working Group for Sarcopenia criteria, and participants will be randomized into either control, RT, VT, or RVT (combined RT and VT) groups. The intervention will last 12 weeks, with assessments performed at baseline, 12 weeks (after intervention), and 24 weeks (follow-up). The primary outcomes will include skeletal muscle mass, handgrip strength, and gait speed. Secondary outcomes comprise IGF-1 concentrations, PI3K/AKT and FOXO3 protein activity, quality of life, and timed-up-and-go test performance assessments.

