## Methods and analysis

### Study design and grouping

This randomized controlled trial will identify the effects of RT combined with VT on the IGF-1/PI3K/AKT/FOXO3 axis in a population with sarcopenia. Participants will be screened for sarcopenia, as defined by the AWGS in 2019, and recruited based on eligibility criteria. Fig 1 summarizes the participant’s enrollment process, interventions, and assessment schedule. Once informed consent is received, the participants will be randomly categorized into (1) control, (2) RT, (3) VT, and (4) combined RT and VT (RVT) groups. Intervention will last 12 weeks, with data collection and assessments at baseline, 12-week (after intervention), and 24-week (follow-up). The 12-week intervention duration was selected based on existing literature indicating that this time frame is sufficient to induce meaningful improvements in muscle mass, muscle strength, and molecular signaling among older adults. Prior studies on resistance and vibration training for sarcopenia typically range between 8–12 weeks, with 12 weeks allowing both early neural adaptation and later-stage hypertrophy to manifest [41–43]. The 24-week time point (i.e., 12weeks post-intervention) was included to evaluate the sustainability of training-induced benefits. Similar follow-up durations have been adopted in previous sarcopenia trials to assess the persistence or decay of functional gains after supervised training ends [44]. Muscle strength, mass, physical performance, FOXO3 protein expression levels, and quality of life will be assessed in all participants. Fig 2 depicts the study design, and S1 File contains the SPIRIT checklist.

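### Read as written, the mixed model for secondary outcomes assumes equal variances and correlations at all visits, so week-12 and week-24 contrasts may carry wrong standard errors

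*Protocol article*

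**What the plan says.** The Statistical analysis section treats the two tiers of outcome differently. Primary outcomes go to a two-way repeated-measures ANOVA. For the rest, "To better accommodate repeated measures and potential within-subject correlations in secondary longitudinal outcomes, linear mixed-effects models will be used", and the model is described as "incorporating random intercepts for participants and fixed effects for time, group, and their interaction". No random slope and no residual covariance structure is named. Confidence intervals are to come from model-based standard errors or from a BCa bootstrap, depending on distributional assumptions.

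There are three visits: baseline, week 12 (end of training) and week 24 (12 weeks after training ends). Study design and grouping gives week 24 its own purpose, which is to see whether gains last. The outcomes concerned are IGF-1, the PI3K/AKT and FOXO3 measures, timed-up-and-go and SF-36.

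**The concern.** A random intercept with independent residuals is the compound-symmetry model: one variance at every visit and one correlation for every pair of visits. The variance of a change score is then the same whether the change spans baseline to week 12, baseline to week 24, or week 12 to week 24.

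This design gives reason to doubt that. The visits are 12 or 24 weeks apart, and training occupies only the first interval. Participants may also respond to training by different amounts, and that response may or may not persist. If change scores truly differ in variance, the pooled error is too small for some contrasts and too large for others. The contrasts at stake are those behind statements that one group gained more than another by week 12, or still held the gain at week 24. They include the signalling-pathway outcomes that are the trial's mechanistic focus.

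**Working it through.** **Inputs from the protocol.** Three visits; four groups; 24 per group ("we plan to recruit 96 individuals (24 per group) to ensure adequate statistical power"); 20% dropout. The 0.05 level is stated for primary tests ("Statistical significance will be defined as p < 0.05 for all primary tests"); I carry it over to the secondary contrasts and take it as two-sided.

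**Inputs assumed.** Between-visit correlations and visit-specific standard deviations, because the protocol gives none. I therefore vary the pattern itself as well as one correlation within it.

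**Formulae.** Let V(i,j) be the true variance of the change between visits i and j. The compound-symmetry model gives every change score the mean of the three:

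M = [V(0,12) + V(12,24) + V(0,24)] / 3

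With R = √(V/M) for the contrast of interest:
- actual level of a nominal 5% test = 2Φ(−1.96/R)
- interval width relative to the correct width = 1/R

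**Worked example: correlations 0.8 (0–12), 0.8 (12–24), 0.64 (0–24), unit variances.**
- V(0,12) = V(12,24) = 2(1 − 0.8) = 0.40, and V(0,24) = 2(1 − 0.64) = 0.72.
- M = 1.52/3 = 0.507.
- Week 24: R = √(0.72/0.507) = 1.192, so the level is 2Φ(−1.644) = 10.0% and the width factor is 0.84.
- Week 12: R = √(0.40/0.507) = 0.889, so the level is 2Φ(−2.206) = 2.7% and the width factor is 1.125.

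**Across patterns** (pairwise group difference in change from baseline):

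| Assumed pattern | Week 12: level, width | Week 24: level, width |
|---|---|---|
| Equal correlations (the model is right) | 5.0%, 1.00 | 5.0%, 1.00 |
| Autoregressive 0.3 | 4.0%, 1.05 | 7.1%, 0.92 |
| Autoregressive 0.5 | 3.4%, 1.08 | 8.4%, 0.88 |
| Autoregressive 0.8 | 2.7%, 1.125 | 10.0%, 0.84 |
| Autoregressive 0.95 | 2.5%, 1.15 | 10.7%, 0.82 |
| Mild decay: 0.7, 0.7, 0.6 | 3.9%, 1.05 | 7.4%, 0.91 |
| Baseline and week 24 most alike: 0.6, 0.6, 0.8 | 7.4%, 0.91 | 1.1%, 1.29 |
| Week-12 SD 30% larger, all correlations 0.7 | 6.3%, 0.95 | 2.5%, 1.14 |
| Response variance 0.3 at week 12, gone by week 24* | 7.0%, 0.93 | 1.6%, 1.22 |
| Response variance 0.2, fully persisting* | 6.5%, 0.94 | 6.5%, 0.94 |

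*Baseline variance 1, correlation 0.8 apart from the response, same in every group. For the first of these, V = 0.7, 0.7 and 0.4, so M = 0.6; for the second, V(0,12) = V(0,24) = 0.6 and V(12,24) = 0.4, so M = 0.533.

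**Simulation checks.** With 24 per group, complete data and 2 × 4 × 23 = 184 error degrees of freedom (20,000 trials), equal correlations gave 5.2% (week 12) and 5.1% (week 24). Autoregressive 0.8 gave 2.5% and 9.6%. REML random-intercept fits at autoregressive 0.8 with 20% monotone dropout (4,000 trials) gave about 3% and 9%. The omnibus group-by-time test stayed between 5.1% and 6.7% in every pattern simulated.

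**The alternative.** With complete data, an unstructured covariance tests each change contrast against that contrast's own pooled variance (96 − 4 = 92 degrees of freedom), so the level should be 5% whatever the pattern. Simulated with complete data in seven patterns, both contrasts ran at 4.8–5.2%. The unstructured fit was not simulated with dropout.

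**The case against.** Four points can be made for the plan.

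1. **The text does not say that random intercepts are the only covariance component.** A random intercept can sit beside a structured residual, and a journal article may leave that to the analysis plan. This stands as a caveat. But the article does more than stay silent: it names a specific structure, and an analyst who follows the sentence literally gets compound symmetry.

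2. **The direction is unknown.** A reader might infer that the plan roughly doubles the false-positive rate at week 24 and costs power at week 12. The documents do not support that as a general statement. It needs correlation that decays with time, with autoregressive correlation of about 0.8 or more for the doubling. The last four rows of the table show week 12 anti-conservative instead, and in three of them week 24 conservative. Those patterns are plausible, because training stops at week 12 and the protocol itself asks whether gains persist or decay. This objection stands, so the finding is stated conditionally. It does not rescue the model: nobody can know beforehand which pattern will hold.

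3. **The reach is limited.** A reader might also infer that every secondary result is compromised. That is not so: the omnibus interaction test is barely moved, and the primary outcomes are analysed by another method. This stands.

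4. **Bootstrap intervals could avoid the problem.** If whole participants are resampled, BCa intervals would not inherit the pooled error. But the bootstrap is conditional on distributional assumptions, the resampling unit is not stated, and it would not correct the model's p-values.

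**Conclusion.** The point holds in a limited, conditional form. Taken literally with independent residuals, the specified model gives all change contrasts one pooled error, and visit-specific group comparisons of secondary outcomes are miscalibrated whenever variances or correlations differ between visits.

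Under decaying correlation (autoregressive 0.3 to 0.95), a nominal 5% week-24 test runs at about 7–11% and week-12 intervals are 5–15% too wide. With baseline and week 24 most alike, or greater variance at week 12, week 12 runs at about 6–7.5% and week 24 at about 1–2.5%. All of these sizes rest on assumed correlations and variances, a common covariance across groups, and a two-sided 5% level. Severity is minor: secondary outcomes only, single-visit contrasts only, unknown direction, and an omnibus test that stays at about 5–7%.

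**What to change.** In the Statistical analysis section, keep the fixed effects of time, group and their interaction, and replace the random intercept with an unstructured 3 × 3 covariance over the visits. Use small-sample degrees of freedom (Satterthwaite or Kenward–Roger). Name in advance one simpler structure, such as the random-intercept model, to be used only if the unstructured model does not converge. If the BCa bootstrap is kept, state that participants are the resampling unit.

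The cost is one or two sentences and four more covariance parameters (six instead of two), which is small with 96 participants and three visits. Trial registration and status reports recruitment as still open, so the change can be made before the final analysis.

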#### Secondary outcomes.

IGF-1 concentrations will be assessed *via* an enzyme-linked immunosorbent assay (ELISA) kit (IGF-1 600 ELISA; DRG, Germany). Blood will be collected from the antecubital vein in a fasting state in serum separator tubes, centrifuged for 15 minutes at 3000 × g and 4°C to harvest serum, which will be stored at −80°C for biochemical analysis [57].

The PI3K/AKT signaling pathway and FOXO3 protein activity will be assessed using immunoblotting (Western blot) and cell isolation assay on specimens obtained via muscle biopsy. Muscle biopsies will be collected at three time points: baseline (pre-intervention), 12 weeks (post-intervention), and 24 weeks (follow-up), enabling longitudinal analysis of the IGF-1/PI3K/AKT/FOXO3 axis. Although more frequent sampling could provide a finer-grained understanding of molecular responses, ethical and practical concerns regarding repeated invasive procedures in older adults limit the feasibility of acute or intra-intervention biopsies in this study. The percutaneous muscle biopsy technique will be employed for lateral femoral muscle biopsy. Briefly, after 2–3 mL of 1% dimethocaine local anesthesia, aspiration will be performed. Then, about 50 mg of muscle tissue lacking blood vessels and connective tissues will be dissected. The samples will be immediately placed in cryotubes, frozen in liquid nitrogen, and stored at −80°C [58].

Then, the protein content will be evaluated *via* the bicinchoninic acid assay (BCA) method (Pierce, Appleton, WI, USA). Subsequently, equal amounts of protein will be subjected to 12% SDS-PAGE gel electrophoresis and transferred onto PVDF membranes, which will then be treated at 4°C with the primary antibodies against PI3k (ab140307,1:1000, Abcam, UK), Akt (SAB4500797, 1:1000, Sigma, USA), Akt (phospho T308) (ab38449, 1:1000, Abcam, UK), and FOXO3 (SAB2107951, 1:1000, Sigma, USA) overnight. Next, the membranes will be flushed with phosphate-buffered saline with tween (PBST), probed with the HRP-linked specific goat anti-rabbit IgG secondary antibody (ab150077, 1:3000, Abcam, UK) for 2 h at ambient temperature, and then washed thrice with PBST. The bands will subsequently be quantified *via* the Image Lab system (Bio-Rad, Shanghai, China) [59,60]. The above analyses will be performed in the Sports Medicine Key Laboratory of Sichuan Province.

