### Data collection and quality control

Before randomization, the characteristics of all the participants will be acquired during baseline evaluations. No data or information will be shared with third parties. Each participant will receive a unique identifier to ensure anonymity, and only personnel conducting statistical analyses will have access to the study database.

All investigators will undergo a comprehensive training program covering the intervention methods for each group, eligibility criteria, trial protocols, outcome measures, and accurate data recording. All practitioners will be certified rehabilitation therapists with at least 3 years of clinical experience in sports rehabilitation.

To increase adherence, participants will receive timely visit reminders and will incur no costs for assessments or treatments. Those who complete all study procedures will receive financial compensation.

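### The mixed model for the secondary outcomes, read naturally, leaves each arm its own baseline mean; it is unbiased but loses (1 − ρ)/2 of the information on the week-12 effect

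*Protocol article*

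**What the plan says.** All references are to the protocol article.

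- **Model.** Under Statistical analysis, the outcomes of secondary rank that are measured repeatedly get a mixed model, described as "incorporating random intercepts for participants and fixed effects for time, group, and their interaction". The article attaches no baseline covariate and no common-baseline constraint to this model.
- **Levels of time.** These are spelled out only for the primary repeated-measures ANOVA, "with factors including time (baseline, 12 weeks, 24 weeks) and group (control, RT, VT, RVT"). The secondary pathway measures follow the same schedule: "Muscle biopsies will be collected at three time points: baseline (pre-intervention), 12 weeks (post-intervention), and 24 weeks (follow-up").
- **Covariates.** A separate sentence says: "Sex, along with baseline IGF-1, age, and muscle mass, will be included as covariates in analysis of covariance (ANCOVA) models". It does not say which outcomes those models serve. Of the secondary outcomes, only IGF-1 has its own baseline in that list.
- **Timing of baseline.** Data collection and quality control states: "Before randomization, the characteristics of all the participants will be acquired during baseline evaluations". Randomization and blinding describes simple, unstratified 1:1:1:1 allocation.

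**The concern.** Baseline is measured before allocation, so the expected baseline means of the four arms are equal by design. A model with free group, time and group-by-time effects over three visits that include baseline does not use this fact. It estimates four separate baseline means and subtracts each arm's own estimate from its week-12 mean. The noise of the baseline measurement then enters the treatment contrast in full. When ρ is below 0.5, such a change score is noisier than ignoring baseline altogether.

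The pathway outcomes carry the mechanistic hypothesis set out in the Introduction. They rest on three biopsies per participant, and the Secondary outcomes section says that more frequent sampling is limited on ethical and practical grounds. With 24 per arm before dropout, any precision that the analysis can recover from data already collected is worth having.

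**Working it through.** **The plan's own figure.** The article gives no precision or power figure for the secondary outcomes and no ρ. Its only related figure is the minimum sample size of 73, "with a significance level of α = 0.05", power "0.80, and four intervention groups (Control, RT, VT, RVT") and f = 0.40. A one-way noncentral F on the 12-week change, with noncentrality 0.40² × N and 3 and N − 4 degrees of freedom, gives power 0.799 at N = 72 and 0.805 at N = 73. So 73 is reproduced, but before dropout: 73/0.80 = 91.25, rounded up to 92, still below the planned 96. Nothing below depends on this.

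**Inputs.** From the article: four arms, 24 per arm, visits at baseline, 12 and 24 weeks, 20% dropout (24 × 0.80 = 19.2, so 19 followed per arm). Assumed: unit variance at each visit, and one correlation ρ between any two visits, which is what a random intercept implies. ρ is set to 0.2, 0.5 and 0.8 for illustration.

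**Step 1. Complete data, difference between two arms at week 12.**

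- Planned interaction contrast (difference in mean change): variance = (2/24) × 2(1 − ρ).
- Common baseline mean, or own baseline as covariate: variance = (2/24) × (1 − ρ²).
- Information lost = 1 − (1 − ρ²)/[2(1 − ρ)] = 1 − (1 + ρ)/2 = (1 − ρ)/2.

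| Assumed ρ | Planned variance | Adjusted variance | Information lost |
|---|---|---|---|
| 0.2 | 0.133 | 0.080 | 40% |
| 0.5 | 0.083 | 0.0625 | 25% |
| 0.8 | 0.033 | 0.030 | 10% |

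A generalized least squares calculation with four arms, three visits and compound symmetry gives the same variances.

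**Step 2. Dropout.** Suppose 24 per arm have a baseline and 19 have both follow-up visits. The mixed model keeps the baselines of those who leave.

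- Planned: variance = 2[(1 − ρ²)/19 + (1 − ρ)²/24].
- Common baseline: variance = 2(1 − ρ²)/19.

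| Assumed ρ | Planned variance | Adjusted variance | Information lost |
|---|---|---|---|
| 0.2 | 0.154 | 0.101 | 35% |
| 0.5 | 0.100 | 0.079 | 21% |
| 0.8 | 0.041 | 0.038 | 8% |

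**Step 3. What this means for power.** This is an illustration only: a true difference of 0.8 SD between two arms, 24 per arm, complete data, two-sided 5% without multiplicity adjustment, noncentral t with 46 degrees of freedom.

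| Assumed ρ | Planned | Adjusted |
|---|---|---|
| 0.2 | 57% | 79% |
| 0.5 | 77% | 88% |
| 0.8 | 99.0% | 99.5% |

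**Step 4. The other contrast that the same model can give.** If the analyst compared raw week-12 arm means from the unconstrained model, the variance in complete data would be 2/24 = 0.083. The loss against the adjusted contrast is 1 − (1 − ρ²) = ρ²: 4%, 25% and 64% at ρ = 0.2, 0.5 and 0.8. For ρ above 0 and below 1, neither contrast is as precise as the adjusted one.

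**The case against.** A random-intercept model with time, group and their interaction is standard and valid. A reader might infer from this point that the secondary results would be biased or their type I error inflated. The documents do not support that: under randomization the planned contrast is unbiased, and only its precision suffers.

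The article also does not say that baseline is a level of time in the mixed model, nor which contrast will be reported. Weeks 12 and 24 alone, with baseline as covariate, would also have time, group and interaction terms. This stands: the reading used here is an inference. It is the natural one, because the same paragraph defines time with three levels and the biopsies follow that schedule. If the authors intend the other model, the fix merely states it.

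A reader might also infer that no secondary outcome is adjusted for its baseline, or that sex and age are kept out of these models. That goes too far. The ANCOVA sentence names no outcomes, so IGF-1 may already be adjusted for its own baseline, and sex and age may enter too. What remains is that the own baselines of PI3K/AKT, FOXO3, timed-up-and-go and SF-36 are not listed.

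Finally, 40% might be read as a ceiling or as a figure for this trial. It is neither. It is the value at an assumed ρ of 0.2; for ρ of 0 or more the limit is 50%. A low ρ is plausible for single-biopsy blots but is an assumption, and it need not carry over to timed-up-and-go or SF-36.

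One might add that baseline handling belongs in an analysis plan that is not shown. But the article does state a specific model, and that model as worded leaves out a free gain.

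**Conclusion.** The point holds as a matter of efficiency for secondary outcomes. On the natural reading, the stated model discards (1 − ρ)/2 of the information on the week-12 interaction contrast: 40%, 25% and 10% at assumed ρ of 0.2, 0.5 and 0.8 with complete data, and about 35%, 21% and 8% with 19 of 24 per arm followed. A comparison of raw week-12 means would lose ρ² instead.

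The result rests on three assumptions: baseline is a level of time in the mixed model, the correlation between visits is constant as a random intercept implies, and ρ lies somewhere in the range shown. If ρ is high, the gain is small. The protocol makes no power claim for these outcomes that this would overturn.

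**What to change.** In the secondary mixed model, either constrain the four arms to a common baseline mean (drop the group main effect; keep time and group-by-post-baseline-visit terms), or model weeks 12 and 24 only, with the outcome's own baseline value as covariate. Include sex and age as fixed effects. State that the week-12 and week-24 differences between arms will be reported from that model.

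The cost is one sentence of wording and a few degrees of freedom. No new data are needed, since baseline values, sex and age are already part of the plan. The article describes enrolment as continuing, so the change can be fixed before the data are unblinded.
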